Non-surgical treatment of low-grade endometrial malignancies with morbid obesity and comorbidities has been directed at restoring the oestrogen-progesterone balance, typically through the addition of progestins. This strategy is often effective but commonly associated with depression and secondary weight gain, which are problematic in the obese. There are no large published case series however reporting on such medical management as primary treatment (feMMe study in progress) and the literature is often focused on younger women who desire fertility preservation^33^ which makes it difficult to apply to the older obese endometrial cancer population. Furthermore these therapies do little to relieve the cardiovascular and endocrine consequences of morbid obesity^37^.

Very Low Calorie Diets (VLCDs), however, can provide safe rapid weight loss in the period immediately preceding surgery and may reduce the perceived perioperative difficulties associated with anaesthetic and surgical techniques. This method of short-term dietary therapy is often overlooked despite being an evidence-based practice supported by the Dietitians Association of Australia (DAA). VLCDs provide 800kcal per day and rank second after bariatric surgery in their ability to help overweight or obese adults lose weight (14.7% mean weight loss at 4-20 weeks) (NHMRC 2006). Patients with a BMI ≥35 can be expected to lose 1.5-2.5kg per week^23^.

VLCDs safely and effectively achieve significant reductions in body weight, liver volume and visceral/subcutaneous adipose tissue. Interestingly 80% of the reduction in liver volume occurs in the first 2 weeks of a VLCD^22^ (see Figure 1). Many of the metabolic and physiologic effects of VLCDs are also beneficial, such as improvement in insulin sensitivity and fasting plasma glucose levels enabling a reduction or even cessation of diabetic medications, lowering of blood pressure and serum triglyceride values ^23,24^. VLCDs are also conducive to ketosis, which can help suppress hunger and preserve lean muscle tissue^23^.

[figure not shown]

Figure 1: Relative changes in liver volume, visceral adipose tissue and body weight during a 12-week very low calorie diet as measured by serial MRI^22^.

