**1.2 Rationale for performing the study**

The rationale of the study is to document the feasibility, tolerability and efficacy of a Very Low Calorie Diet (VLCD) with Optifast in obese endometrial cancer patients by assessing compliance and weight loss. A secondary objective is to measure patients’ metabolic profiles prior to, and following, the intervention to provide data to inform further research.

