**2.2 Secondary Outcomes**

Secondary outcomes will include:

-Monitoring changes over the 4-6 week VLCD period in body weight, BMI, anthropometric measures (hip and waist circumference), blood pressure and serum biochemistry.

-Evaluating patient tolerability of the VLCD using a validated qualitative questionnaire.

-Collecting data on surgical outcomes.

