**3 STUDY DESIGN**

**3.1 Design and study group**

This is a prospective observational study investigating obese (BMI ≥ 35) women with low risk (early stage, low grade endometrioid histology) endometrial cancer planned to undergo laparoscopic hysterectomy.

In addition to the routine information obtained from the initial visit history form (see appendices 10.1), the following information will be recorded:

- Geographical location (rural or local)
- Histology at diagnosis
- Any current non-surgical treatment for endometrial cancer (e.g. Mirena or Provera)
- Any previous history of weight loss, pharmacotherapy or enrolment in weight control programs and amount of weight lost and for how long

The pre-operative Very Low Calorie Diet will be with Optifast® and involves a 4-6 week ‘Intensive Phase’, 800 kcal (<3,300kJ) per day containing all RDI of protein, carbohydrate, essential fatty acids, fibre, vitamins, minerals and trace elements. 3 Optifast VLCD products must replace regular main meals (shakes, soups, desserts or bars). A Minimum of 2 cups of low starch vegetables are allowed per day in addition to 1tsp oil per day to help the gallbladder contract in the absence of additional fat in the diet. A minimum of 2L water and other calorie free beverages each day is allowed. Alcohol consumption is discouraged during the VLCD, however, if this is too difficult for patients, then 1-3 standard drinks per week is the maximum allowed.

As part of this particular research project, participants will have their dietary compliance assessed by urine tests, tolerability of the Optifast diet assessed by questionnaires, additional body measurements and blood tests performed.

Urinary ketone reagent strips will be used to assess dietary compliance. After the first week of a VLCD, an increase in the urinary excretion of ketoacids occurs subsequent to increased fat catabolism; therefore the presence of at least trace ketones in the urine is considered to indicate net lipolysis and dietary adherence^22,30^. Urine samples are to be collected fortnightly at the dietitian or local GP consultation. The absence of ketones is scored 0, trace 1, small amount 2, moderate amount 3. Ketone scores determined at visits every 2 weeks will be summed for each patient.

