A validated questionnaire of product side effects and acceptability^22^ will be used. Subjects will be asked to rate 6 factors of product taste, hunger, nausea/vomiting, bowel function, emotional eating and social eating on a 5 point Likert scale (see appendices 10.2).

Anthropometric measurements of height (using a wall-mounted stadiometre), weight (wearing light clothing, no shoes), BMI (weight kg/height m^2^), waist circumference (narrowest point between low rib margin and iliac crest) and hip circumference (widest point over greater trochanters) will be recorded at baseline and fortnightly preferably by the same clinician or their appropriate delegate. Seated blood pressure will be measured at baseline and fortnightly. Blood tests will be taken at baseline and again on the day of surgery (after 4-6 weeks of Optifast) including FBC, EUC, LFTs, CMP, uric acid, CA125, iron studies, fasting lipid profile (Total cholesterol, LDL, HDL, TG), fasting glucose metabolism (plasma glucose, plasma insulin, HBA1C) and 25OHVitD.

All patients will be given instructions on pre operative fasting and be allowed clear fluids up to 2 hours and solids up until 6 hours prior to induction of anaesthetic as per ERAS recommendations. Randomized controlled trials on mechanical bowel preparation have shown no improvement in surgical exposure or bowel handling in laparoscopic gynaecologic procedures^34-35^.

For the laparoscopic hysterectomy, all patients will receive 2g Cephazolin and 500mg metronidazole 15-60 minutes prior to skin incision (as per eTG 2006). Clindamycin (or Lincomycin) 600mg can be used for patients who are allergic to penicillin.

Additional information will be recorded post operatively on:

- Tumour stage, grade, histological type, degree of myoinvasion
- Lymphadenectomy performed – Yes or No
  - Pelvic vs. para-aortic nodes
  - Sentinel lymph node biopsy vs. debulking of enlarged nodes vs. full pelvic lymph node dissection
  - Number of nodes removed
  - Number of nodes positive
- Adjuvant treatment recommendation from multidisciplinary meeting/tumour board
- ASA and Anaesthetic time
- Operating time
- Surgical complications – urinary tract, vascular or bowel injury; cardiac/pulmonary complications; wound breakdown; infection; estimated blood loss
- Length of hospital stay

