**5.3 Study Procedure Risks**

Optifast VLCD is accepted as being safe with only minor transient side effects generally insufficient in duration or magnitude to warrant cessation. The main side effects of rapid weight loss and ketosis include cold insensitivity, halitosis, headache, alopecia, irritability, postural hypotension, fatigue, muscle cramps, bowel disturbance (constipation or diarrhoea).

Patients are still eligible for Optifast although extra care should be taken if there is a history of cholelithiasis, pancreatitis or gout as these conditions may flare during rapid weight loss.

Additionally the use of the VLCDs may influence the dosage requirements of some medications, however, patients on sulphonylureas, short and long acting insulins, diuretics for hypertension, medications for hyperlipidaemia, and warfarin are still eligible under medical supervision.

In Australia cancer surgery is normally assigned a clinical urgency Category 1 or 2 which means surgery is performed within 30-90 days of being added to a wait list (AIHW). The 4-6 week time frame will be at the discretion of the Gynaecologic Oncologist.

Venipuncture carries the small risk of swelling, tenderness, or inflammation at the site, vasovagal, infection and thrombosis.

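### Drug doses may change during the diet but are recorded only at or before enrolment, so the secondary before-after changes in blood pressure, glucose, insulin, HbA1c and lipids may mix diet and drug-change effects

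*Protocol*

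**What the plan says.** Section 5.3 states that "the use of the VLCDs may influence the dosage requirements of some medications". It adds that patients on sulphonylureas, "short and long acting insulins, diuretics for hypertension, medications for hyperlipidaemia, and warfarin are still eligible under medical supervision". Section 1.1 lists among the benefits of these diets better insulin sensitivity and fasting glucose, "enabling a reduction or even cessation of diabetic medications, lowering of blood pressure and serum triglyceride values".

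The secondary outcomes in section 2.2 are changes over the diet in weight and body measurements, "blood pressure and serum biochemistry". Section 3.1 gives the detail. "Blood tests will be taken at baseline and again on the day of surgery", and the panel includes plasma glucose, plasma insulin, HbA1c and four lipids (total cholesterol, LDL, HDL and triglycerides). Seated blood pressure is taken at baseline and fortnightly. Section 1.2 gives the purpose: to measure "metabolic profiles prior to, and following, the intervention to provide data to inform further research".

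Medication is mentioned as something to record or check in three places. Section 5.4 has it checked at screening. The initial visit form in section 10.1 has a heading for it. Section 3.1, in the list that opens "In addition to the routine information obtained from the initial visit history form", asks for current non-surgical cancer treatment and any past pharmacotherapy. All three fall at or before enrolment.

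**The concern.** The drug classes named in section 5.3 act on the measures that section 2.2 follows. If a woman's insulin or diuretic is cut because the diet is working, her glucose or blood pressure on the day of surgery may look much as it did at baseline. Her record would show little change, when the true result is similar control on less medication. A dose increase would mislead the other way and credit the diet with an effect of the drug.

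The study has one group and no control, so nothing else in the design separates the two effects. Two things are at stake. One is the meaning of several secondary outcomes that are meant to inform later research. The other is a result the protocol itself counts as beneficial, fewer or lower doses of diabetic drugs, which the planned data cannot report. An analysis plan cannot repair this, because it cannot describe doses that were never collected.

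**Working it through.** The protocol gives no figure to reproduce: section 7.1 calls the sample size pragmatic and the analysis descriptive. The check is a comparison of what may change with what is recorded.

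**Step 1. Which drugs meet which outcomes.** Counting insulins as one class, section 5.3 names five.

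| Class in 5.3 | Planned measure it acts on |
| --- | --- |
| Sulphonylureas | glucose, insulin, HbA1c |
| Insulins | glucose, insulin, HbA1c |
| Diuretics for hypertension | blood pressure |
| Lipid drugs | total cholesterol, LDL, HDL, triglycerides |
| Warfarin | none of these |

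Four of the five classes bear on a planned secondary measure.

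**Step 2. Where drugs or doses are recorded.**

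| Place in the protocol | Drug or dose item | Timing |
| --- | --- | --- |
| 5.4 screening | current medications checked | before enrolment |
| 10.1 initial visit form | medications heading | initial visit |
| 3.1 baseline list | non-surgical cancer treatment; past pharmacotherapy | baseline |
| 5.1 flow chart | none | – |
| 5.2 schedule, 7 rows by 5 columns | history row, ticked in 1 column | enrolment visit |
| 3.1 list opening "Additional information will be recorded post operatively on" | none | – |

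In section 5.2, 0 of 7 rows record a drug or dose after enrolment. That count is not enough alone, because the schedule also omits operating time and complications, which section 3.1 does collect. The other lists were therefore checked too, and none has a drug item during the diet or on the day of surgery. The summary uses the discharge summary for the post-operative course and says in general terms that clinical data will be recorded; neither names doses during the diet.

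**Step 3. Direction.** For a woman whose drug changes, observed change = diet effect + effect of the drug change. When a drug is reduced, the second term tends to raise glucose, blood pressure or lipids, so the observed fall is smaller than the diet effect. When a drug is increased, the sign reverses.

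**Step 4. Size.** With n = 20 women, of whom k have a relevant dose change and each is shifted on average by d, the mean change shifts by k × d / 20. One affected woman moves the mean by 1/20 = 5% of her own shift; with k = 0 the shift is zero. The value of k would differ between glucose, blood pressure and lipids, since each depends on its own drug class. The documents give neither k nor d, nor the share of women on these drugs, so no figure follows.

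**The case against.** The strongest reply has four parts.

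- **The premise can be pushed too far.** A reader might infer that the protocol expects doses of glucose, blood pressure and lipid drugs to change. It does not say so. Section 5.3 says only that the diet may influence requirements. Section 1.1 speaks of reducing drugs for diabetes alone; it mentions blood pressure and triglycerides as values that fall. This stands: for blood pressure and lipid drugs the support is a possibility.
- **The outcomes are secondary and descriptive.** Section 1.2 ties feasibility, tolerability and efficacy to compliance and weight loss, and the primary outcome is ketone-based compliance. Change under the diet plus ordinary drug management is a legitimate thing to describe, and without a control group attribution is limited anyway. This lowers the weight of the point but does not remove it: without dose records a reader cannot tell what the described change consists of.
- **Some information exists.** Baseline medication is captured, so women not on these drugs at entry can be identified and described, and routine notes may hold some dose changes. This stands in part. Follow-up may be with a local GP or by phone, so those notes may sit outside the hospital, and the protocol does not plan to collect them.
- **Analysis detail may sit in a statistical analysis plan.** True of how results are tabulated, but not of data collection.

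**Conclusion.** The gap in recording is confirmed from the text and needs no assumption. The protocol says doses may change, keeps the users of these drugs in, follows the measures those drugs act on, and records no dose after enrolment. The before-after changes in blood pressure, glucose, insulin, HbA1c and lipids may therefore mix diet and drug-change effects, most likely understating benefit where drugs are reduced, and drug reduction itself goes unreported.

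A distortion arises only if some women change dose. Its size cannot be derived from the documents, and any statement that a given share of the diet's effect is hidden would only restate assumed inputs. A reader might also infer that the feasibility result is undermined or that the later trial would be wrongly sized. The documents do not support either: the ketone outcome and weight lie outside this point, and section 7.1 does not say which measure would set that trial's sample size. This is a cheap improvement worth making, and does not put the study's main purpose in doubt.

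**What to change.** Add one row to the section 5.2 schedule: current dose of each drug in a class listed in section 5.3, with the date of and reason for any change. Tick it at the start of the diet, week 2, week 4 (6-week programme) and the day of surgery.

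In section 7.1 or the analysis plan, state that the report will give the number of women with a relevant drug reduced, stopped or increased. Describe changes in blood pressure, glucose, insulin, HbA1c and lipids for all women and by use of a relevant drug at baseline (users and non-users), with the dose changes listed alongside. Do not use a subgroup chosen for having had no drug change: that selects on an event after baseline, and if drugs are cut because the diet works it would leave out the users who responded best.

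The cost is one form row at contacts that already take place (3 in the 4-week programme, 4 in the 6-week programme) and one small descriptive table. Some of those contacts may be by phone, where doses can still be asked. No visit, test, entry criterion or surgery date changes, and dosing decisions stay with the treating doctors. With 20 women the user and non-user groups will be small, so their figures stay descriptive.

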**5.4 Recruitment and Screening**

Women recommended to have a VLCD as part of pre-operative preparation for surgery will be invited to participate. The consultant gynaecological oncologists accredited at SJOG Subiaco Hospital will identify them at their initial visit. A study coordinator will screen patients who are interested in participating. Patients’ medical history, current medications and BMI will be checked to ensure that all inclusion criteria are met and there are no exclusion criteria apparent. A patient information package and consent form will be given to the patient to read. The potential participant, if agreeable, will sign a written consent form for the study at the time of consenting to the laparoscopic surgical procedure. If they wish to have additional time to read the patient information package before making a decision to participate, a follow-up phone call addressing further questions and if they wish to participate will be made. It will be made clear to each participant that if they do not wish to participate or withdraw from the study, their ongoing care will not be affected.

**5.5 Informed Consent Process**

The patient will have adequate time to read the patient study information package and to ask any questions or concerns about the study. If they agree to participate, the treating team will gain their written consent at the time of the surgical consent. A follow-up phone call will be made to any potential participant who wishes to have further time to consider the study and consents to receive the call.

**5.6 Enrolment Procedure**

The participant will be enrolled into the study after the informed consent process has been completed and the participant has met all inclusion criteria and none of the exclusion criteria are apparent. The participant will receive a study enrolment number and this will be documented on the patient’s medical record and on all study documents.

**6 SAFETY**

**6.1 Study processes**

The collecting of blood will be by the usual processes ensuring sterility of patient/blood collector safety.

The transport of tissue samples from the operating theatre to Clinical Labs laboratory will be by the usual processes meeting all requirements for human tissue specimen collection.

**6.2 Data safety and monitoring**

## After the first 6 months of the study, the study coordinators will meet with a data monitoring committee to discuss progress and any safety issues relating to the study. If any issues are raised by patients and communicated with investigators in relation to the study, this will be communicated to [name] immediately.

**6.3 National and international guidelines**

Approval for the study will be sought from the St John of God Healthcare Human Research Ethics Committee. Patients will be required to give informed written consent and will be free to withdraw from the study from any time during treatment.

This study will be conducted according to the National and International guidelines pertaining to ethical research on humans. The guidelines of the World Medical Association Declaration of Helsinki: Ethical Principles for Medical Research Involving Human subjects and the NHMRC National Statement on Ethical Conduct in Research involving Humans (2007), will be strictly adhered to at all times during the study.

**6.4 Early termination**

Early termination could occur in the event of poor recruitment, lack of funds, safety concerns or sickness in one of the principle investigators. The principle investigator, [name] would immediately inform HREC and the participants if the study were to be terminated early.

**7 STATISTICAL CONSIDERATIONS**

**7.1 Sample size and analysis plan**

The sample size for this observational, proof of concept study is pragmatic and analysis of will be descriptive. The findings of this study will facilitate calculation of the sample size calculation for a subsequent, appropriately powered, randomized controlled trial. Data analysis will be performed using the statistical software IBM SPSS Statistics Version 20.

**8 STORAGE AND ARCHIVING OF STUDY DOCUMENTS**

Clinical data for each patient will be given a code and de-identified from the patient details. The de-identified data will be kept in an Excel spreadsheet format on a computer, which can only be accessed by a login password unique to the investigators.

At the termination of the study, any paper copies of data will be shredded as per requirements for health related data. De-identified electronic files will be deleted two years after completion of the study as per the SJOG procedure for sensitive medical records. All data will be stored securely and destroyed at 7 years, as per NHMRC guidelines. The data will then be deposed of as per SJOG protocol for destruction of records.

**10 APPENDICES**

**10.1 Initial visit history form.**

**GYNAECOLOGICAL ONCOLOGY**

**PATIENT INFORMATION**

**HISTORY OF PRESENT ILLNESS: Date:**

**BLADDER:**

**BOWELS:**

**A WEIGHT LOSS B Yes, how much (kg)**

No = 0 1-05 - 5kg = 1

Yes = 2 6 – 10kg = 2

Unsure = 2 11 – 15kg = 3

> 15kg = 4

Unsure = 5

**C. EATING POORLY OR LACK OF NUTRITION SCORE**

**APPETITE** If > 2 refer for nutrition

assessment/intervention

No = 0

Yes = 1 **Total score =**

**OBSTETRIC HISTORY:**

**MENSTRUAL HISTORY:**

**Cycle:**

**Menarche:**

**Menopause:**

**Years on OC’s:**

**HRT:**

**ANY PREVIOUS FERTILITY DRUGS:**

**SEXUAL HISTORY:**

**PAP SMEAR HISTORY:**

**MAMMOGRAM:**

**PAST MEDICAL HISTORY:**

**MEDICATIONS**

**PAST SURGICAL HISTORY**

**PREVIOUS CHEMOTHERAPY:**

**PREVIOUS RADIOTHERAPY:**

**CIGARETTES:**

**ALCOHOL:**

**ALLERGIES:**

**FAMILY HISTORY OF SERIOUS ILLNESS/CANCER:**

**SOCIAL HISTORY**

**PHYSICAL EXAMINATION:**

**General Appearance:**

**Performance Status:**

**Height: Weight: BMI:**

**BP:**

**Chest:**

**Heart:**

**Breasts:**

**Abdomen:**

**Peripheral Nodes:**

**PELVIC EXAMINATION:**

**External Genitalia:**

**Vagina:**

**Cervix:**

**Uterus:**

**Adnexae:**

**Rectal:**

**COLPOSCOPY:**

**PROVISIONAL DIAGNOSIS:**

**INVESTIGATIONS:**

**TREATMENT:**

**10.2 Patient VLCD Questionnaire**

**Circle how many weeks of Optifast have you completed?**

| 2 | 4 | 6 |
| --- | --- | --- |

1. **How do you rate the product taste?**

| Highly unacceptable | Unacceptable | Tolerable | Acceptable | Highly acceptable |
| --- | --- | --- | --- | --- |
| 1 | 2 | 3 | 4 | 5 |

1. **How hungry are you?**

| Extreme Hunger | Hungry most days | Hungry some of the time | Occasional Hunger | No Hunger |
| --- | --- | --- | --- | --- |
| 1 | 2 | 3 | 4 | 5 |

1. **How much nausea or vomiting do you have?**

| Daily | 4-6 times/week | 2-3 times/week | ≤1 time/week | None |
| --- | --- | --- | --- | --- |
| 1 | 2 | 3 | 4 | 5 |

1. **How well are your bowels working compared to what is normal for you?**

| no bowel motion in the past 4 days | no bowel movement in the past 2-3 days | normal | increased frequency | diarrhoea |
| --- | --- | --- | --- | --- |
| 1 | 2 | 3 | 4 | 5 |

1. **How often are you emotional eating?** - Emotional eating defined as ‘eating foods outside the diet’s guidelines, due to emotional reasons such as stress, sadness, frustration, anger.

| Daily | 4-6 times/ week | 2-3 times/week | ≤ 1 time/week | None |
| --- | --- | --- | --- | --- |
| 1 | 2 | 3 | 4 | 5 |

1. **How often are you social eating?** - Social eating defined as eating foods outside the diet’s guidelines because you are in a social setting.

| Daily | 4-6 times/ week | 2-3 times/week | ≤ 1 time/week | None |
| --- | --- | --- | --- | --- |
| 1 | 2 | 3 | 4 | 5 |

